### Other variables of interest

• Sociodemographic (age, sex, and race)• Socioeconomic (work and income)• Social capital (number of family and friends)• Quality of life (QoL indicator extracted from the World Health Organization Disability Assessment Schedule 2.0 (WHODAS)) (Ferrer et al., 2019; Üstün, 2010)• Physical activity (leisure-time physical activity (LTPA) indicator extracted from the International Physical Activity Questionnaire (IPAQ)) (Craig et al., 2003).

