### Eligibility

All adults aged 60 and older living in the study area who will be contacted by the study team can participate in the study. Older adults residing in long-stay institutions for the elderly and those who are bedridden will be excluded from our study as the focus of this research is the follow-up of IC until the development of one or more outcomes: severe dependence, fall, hospitalization, or death as a function of IC. It will also be important to ensure through an initial in-house geriatric assessment that participants at baseline do not have significant loss of independence in the activities of daily living (ADL and IADL scores >0) (Katz and Akpom, 1976; Lawton and Brody, 1969) and cognitive ability (Clinical Dementia Rating (CDR) > zero) (Morris, 1994).

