## Research questions and hypotheses to test

This proposed research will answer three scientific questions:1. Whether IC will decrease as expected at the 3-year follow-up (ICI at end-time ≤ ICI at baseline, or ∆IC < 0), regardless of the socioecological context, individual sociodemographic, behavioral, and clinical factors, and comorbidities (Charlson et al., 1987). This research will statistically test the hypothesis that ICI will not change over time (i.e., follow up IC = baseline IC, or ∆IC = 0).2. If DIC (or TIC) at baseline will be a strong predictor of FA, such as ADL (Mlinac and Feng, 2016), IADL (Hokoishi et al., 2001), falls (Kitcharanant et al., 2020), and death, regardless of the socioecological context, individual sociodemographic, behavioral, and clinical factors, and comorbidities (Charlson et al., 1987). That is, whether the proportion of these ADL/IADL losses, falls, and deaths will be greater in the decline group (e.g., DIC present) than in the unexposed group (e.g., DIC absent). Research will statistically test the hypothesis that there is no association between IC and ADL (or IADL) (e.g., relative risk for TIC or DIC and IADL = 1).3. Whether IC and its five domains are directly associated with a measure of QoL (i.e., World Health Organization Disability Assessment Schedule 2.0 (WHODAS 2.0)) (Prüss-Ustün et al., 2017) and LTPA (i.e., the International Physical Activity Questionnaire (IPAQ)) (Craig et al., 2003), regardless of the socioecological context, individual sociodemographic, behavioral, and clinical factors, and comorbidities (Charlson et al., 1987). Research will statistically test the hypothesis that there is no association between IC and either QoL or LTPA (e.g., relative risk for TIC or DIC and LTPA = 1).

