#### Statistical models to assess the question of whether the quality of life (WHODAS 2.0) and leisure-time physical activity (LTPM) are associated with IC

A slope coefficient of IC (Y = 1 if DIC = 1 or more declines, and Y = 0 if DIC = no decline) will be estimated by a logistic regression model as a function of QoL at baseline (WHODAS = 0 (high), WHODAS = 1 (medium), or WHODAS = 2 (low)) adjusted for the influence of other individual factors such as sociodemographic factors (age, sex, education, and health coverage), comorbidities, loss of ADL/IADL, and socioecological factors (e.g., sociability). The set of V and W will be a collection of covariates similar to previous models, repositioning X = 1 for LTPA that reaches the recommended levels and X = 0 for LTPA that does not reach recommended levels and keeping the same collection of V and W. The relationship between LTPA and IC (or DIC), adjusted for other individual socioecological factors, will also be evaluated by logistic regression.

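### Question 3 reports a WHODAS disability indicator as quality of life, in a cohort screened for independence, and cuts that indicator into three classes

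*Protocol article*

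**What the plan says.** The protocol article names its quality-of-life measure in three places:

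- *Other variables of interest* lists a "QoL indicator extracted from the World Health Organization Disability Assessment Schedule 2.0 (WHODAS" instrument. No other quality-of-life measure appears.
- *Research questions and hypotheses to test*, question 3, asks whether intrinsic capacity (IC) and its domains are "directly associated with a measure of QoL (i.e., World Health Organization Disability Assessment Schedule 2.0 (WHODAS 2.0".
- The *Data analysis* subsection on WHODAS 2.0 and leisure-time physical activity models decline in IC (DIC, yes or no) by logistic regression "as a function of QoL at baseline (WHODAS = 0 (high), WHODAS = 1 (medium), or WHODAS = 2 (low". The adjustment set includes "comorbidities, loss of ADL/IADL, and socioecological factors (e.g., sociability". How the three classes are cut is not stated.

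*Eligibility* decides who contributes a baseline value. "Older adults residing in long-stay institutions for the elderly and those who are bedridden will be excluded from our study". It also seeks to ensure that "participants at baseline do not have significant loss of independence in the activities of daily living (ADL and IADL scores >0", and likewise no significant loss of "cognitive ability (Clinical Dementia Rating (CDR) > zero".

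**The concern.** Two things are at stake.

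The first is the name of the result. Question 3 is presented as a question about quality of life, separate from question 2, which concerns ADL, IADL, falls and death. If its only measure is a disability indicator, question 3 lies close to question 2. A positive finding would then be published under a broader label than the measurement supports.

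The second is how to read a null result. The predictor is the baseline value, taken in people selected for independence. A predictor with a narrowed range gives a less precise slope, and grouping it into three classes loses more. A reader who sees no association could not tell absence of a relation from too little spread in the predictor.

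**Working it through.** The protocol gives no sample size, power, score distribution or class share for question 3. Tables 1 and 2 concern functional loss and mortality, so there is no stated figure to reproduce. The check is mainly a comparison of passages, with one illustration.

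**Step 1: the construct.** Three statements in the article, side by side:

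- *Introduction*: good functionality is one of several pillars of quality of life in older people, and limitation and dependence are described as having implications for it. Functioning is thus a component or a cause of quality of life, not the whole.
- *Discussion*: the study's hypotheses are summarised as effects of IC on ADL, IADL and WHODAS. WHODAS stands with the functional measures and is not called quality of life there.
- *Other variables of interest* and question 3: WHODAS is the quality-of-life measure.

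The first two do not support using the third without qualification.

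**Step 2: the range.** *Eligibility* removes bedridden and institutionalised people and those with significant loss of ADL/IADL independence or cognitive ability. If the bracketed conditions (scores above zero) define the loss, the screen is strict. If the word significant governs, it is looser. On either reading the dependent end of a disability score is thinned at baseline. It is not emptied of all impairment: Table 3 still allows for impaired vision, hearing, balance and gait, high pain scores, depressive symptoms and poor sleep, and none of these excludes a person.

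**Step 3: the classes.** With fixed cut-points, the low class could be sparse. With sample terciles, it would hold about a third of the cohort (barring ties), and low would be a relative label among people screened as independent. The documents do not say which applies.

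**Step 4: how much a sparse class would matter.** This is an illustration. The class shares, DIC rates and odds ratios are all assumptions.

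- Initial sample 5,500 and dropout 15% (both from *Study sample size and power calculation*): N = 5,500 × 0.85 = 4,675.
- The low class holds share s. The remainder is split equally between high and medium.
- DIC rate in the high class, p_H: 20%, 30% or 50%. Two-sided alpha 0.05 (the protocol gives 0.05 without sidedness).
- Power (low v. high) = Φ[(|p_L − p_H| − 1.96·SE0)/SE1], with SE0 from the pooled proportion and SE1 from the two separate proportions.

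Example with s = 5%, p_H = 0.20, odds ratio 1.5:

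- Low-class odds = 0.25 × 1.5 = 0.375, so p_L = 0.375/1.375 = 0.2727.
- n_L = 233.75 and n_H = (4,675 − 233.75)/2 = 2,220.6.
- Pooled proportion 0.2069, SE0 = 0.02786, SE1 = 0.03034.
- (0.0727 − 0.0546)/0.03034 = 0.597, so power = 0.725.

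| Share in low class | Power, OR 1.5 | Power, OR 2.0 |
|---|---|---|
| 33% | >0.99 | >0.99 |
| 10% | 0.92–0.98 | >0.99 |
| 5% | 0.73–0.83 | 0.99 or more |
| 2% | 0.41–0.47 | 0.84–0.90 |
| 1% | 0.25–0.28 | 0.60–0.65 |

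Ranges run over the three DIC rates. Power for this contrast becomes a concern only if the low class falls to a few percent.

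**The case against.** The strongest reply has four parts.

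- **Question 3 defines its own measure.** It equates quality of life with WHODAS 2.0 and names the instrument openly throughout. This stands. A reader might infer that question 3 cannot be answered at all, but an association with WHODAS can be estimated. What remains is how far the conclusion may be worded.
- **The construct argument rests on the instrument's name.** The article cites sources for the extracted indicator that are not at hand, so whether WHODAS has been validated as a quality-of-life proxy cannot be judged here. This also stands, and no claim is made about the instrument's items. The mismatch noted is between the article's own statements.
- **The cohort is not free of disability.** A reader might infer that eligibility selects people with none. The text excludes significant dependence and cognitive loss, and Table 3 leaves room for other impairments. Only a probable narrowing is supported.
- **Cut-points may be in a fuller document, and the planned baseline descriptives would show clustering.** The absence of cut-points is therefore not itself a fault. But descriptive plots do not change the three-class predictor written into the model, nor do they commit the report to reading a null result against the observed range.

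One might add that adjusting for ADL/IADL loss separates WHODAS from question 2. It does so only in part. If the covariate is measured at baseline, eligibility leaves it little variation. If it is measured later, it removes variation related to the predictor.

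**Conclusion.** The point holds as one of labelling and efficiency. The quality-of-life half of question 3 measures disability or functioning as WHODAS records it, and a result stated simply as quality of life goes beyond that. The baseline range is probably narrowed by eligibility, and the three-class coding gives up further information for no stated reason.

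The extent of the narrowing cannot be sized from the documents. In particular, a reader might infer that the low class will be nearly empty or pressed against the floor. Without cut-points or a distribution this is not shown, and with terciles the class would hold about a third of participants. The power figures above show what would follow under assumed shares. They do not predict what will happen.

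The effect is limited to one half of one of three research questions. Questions 1 and 2 are untouched.

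**What to change.** 1. In the *Data analysis* subsection on WHODAS 2.0, make the baseline score of the extracted indicator the predictor in the main analysis, with a non-linear term if values cluster at the floor. Keep the three classes for description at most.
2. In *Other variables of interest*, question 3 and that same subsection, state the result as an association with WHODAS-measured disability or functioning, not with quality of life in general.
3. Report the share of participants at the least-disabled end of the score, so that a null result is read with the restricted range in mind.

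The article states that no data have been collected, so the cost is some rewording, one change of covariate coding and one extra descriptive figure. The real price is a narrower quality-of-life claim. If the investigators want the broader claim, they would need to add a separate quality-of-life measure before enrolment, at the cost of some participant burden.

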## Research questions and hypotheses to test

This proposed research will answer three scientific questions:1. Whether IC will decrease as expected at the 3-year follow-up (ICI at end-time ≤ ICI at baseline, or ∆IC < 0), regardless of the socioecological context, individual sociodemographic, behavioral, and clinical factors, and comorbidities (Charlson et al., 1987). This research will statistically test the hypothesis that ICI will not change over time (i.e., follow up IC = baseline IC, or ∆IC = 0).2. If DIC (or TIC) at baseline will be a strong predictor of FA, such as ADL (Mlinac and Feng, 2016), IADL (Hokoishi et al., 2001), falls (Kitcharanant et al., 2020), and death, regardless of the socioecological context, individual sociodemographic, behavioral, and clinical factors, and comorbidities (Charlson et al., 1987). That is, whether the proportion of these ADL/IADL losses, falls, and deaths will be greater in the decline group (e.g., DIC present) than in the unexposed group (e.g., DIC absent). Research will statistically test the hypothesis that there is no association between IC and ADL (or IADL) (e.g., relative risk for TIC or DIC and IADL = 1).3. Whether IC and its five domains are directly associated with a measure of QoL (i.e., World Health Organization Disability Assessment Schedule 2.0 (WHODAS 2.0)) (Prüss-Ustün et al., 2017) and LTPA (i.e., the International Physical Activity Questionnaire (IPAQ)) (Craig et al., 2003), regardless of the socioecological context, individual sociodemographic, behavioral, and clinical factors, and comorbidities (Charlson et al., 1987). Research will statistically test the hypothesis that there is no association between IC and either QoL or LTPA (e.g., relative risk for TIC or DIC and LTPA = 1).

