## Dependent variables

• Need for help in ADL (Katz and Akpom, 1976) and IADL (Lawton and Brody, 1969).• Falls in the last year.• Hospitalizations in the last year.• Deaths.

Explanatory variables: IC domains and subdomain measures.

The IC subdomain measures, their levels, cut off points for a binary classification, and references are presented in Table 3.

**TABLE 3 T3:** Intrinsic capacity domains and subdomains measures with classification cut-offs.

Domain	Subdomain	Classification (binary: 0 or 1)	References
Vitality	Number of chronic morbidities	<2 = 0 | ≥ 2 = 1	Charlson et al. (2022) and Charlson et al. (1987); Kim et al. (2021)
	Number of medications taken daily	0–4 = 0 | 5+ = 1	Golchin et al. (2015)
	Handgrip strength	Men:<=36.2 kg = 0 | > 36.2 kg = 1; Women:<=23.0 kg = 0 | > 23.0 kg = 1	Amaral et al. (2019), Alqahtani et al. (2019)
	Body mass index	≤ 25 = 0 | > 25 = 1	Kiskaç (2022), Krzyminska-Siemaszko et al. (2014)
	Biomarkers of metabolism and inflammation	NL = 0 | high = 1	Liu et al. (2017), Bautmans et al. (2022), Bohannon (2019)
	Pain numerical rating scale (NRS)	≤ 6 = 0 | > 6 = 1	Devin and McGirt (2015), Atisook et al. (2021)
Mobility	Tandem stance	Tandem stance for>=10 s = 0 | tandem stance for <10 sec= 1	Joo et al. (2021)
	Gait (timed up and go)	<6 min = 0 | ≥ 6 = 1	Herman et al. (2011); Alexandre et al. (2012)
Sensory	Community screening for visual impairment	Good = 0 | impaired = 1	Clarke et al. (2018)
	Hearing screening in older adults	Good = 0 | impaired = 1	https://hign.org/consultgeri/try-this-series/hearing
Cognitive	Memory (MOCA)	≥ 25 = 0 | < 25 = 1	Nasreddinne et al. (2005)
	Cognitive abilities (CDR)	0 = 0 | ≥ 0,5 = 1	Morris (1994)
Psychological	Depressive symptoms (GDS)	<5 = 0 | ≥ 5 = 1	Almeida and Almeida (1999), Yesavage et al. (1983)
	Sleep quality	good = 0 | bad = 1	Smyth (2013)

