### Explanatory variables: IC composite index (ICI)

An IC composite score or index (IC index or ICI) will first be created, as suggested by Gutiérrez-Robledo et al. (2019). This score aims to express a summary measure of impairments for an older adult. Initially, each continuous or ordinal subdomain measure will be dichotomized based on acceptable cut-off points to create a binary variable of 0 or 1 (see Table 3 for cutoff points across all subdomain measures). Within a domain, the values of these recoded subdomain measures will be summed up to create a “subdomain score.” The subdomain scores will range from 0 to 2 for the four subdomains with only two measures and from 0 to 6 for the subdomain with six measures (i.e., vitality). Then, each domain of the five IC components will be subdivided into three categories based on the sum of the scores of its subdomains, with the following numerical score: no impairment = 0, mild impairment = 1, and severe impairment = 2. For example, the four domains with only two subdomain measures (e.g., cognitive with subdomain measures memory and cognitive) will be coded 0 if their subdomain score (sum of their subdomain measure) is 0, 1 if the subdomain score value is 1, and 2 if the subdomain score value is 2. The domain with six subdomain measures, vitality (subdomains comorbidity, medication, biomarkers, pain, strength, and nutrition), will be coded 0 if its subdomain score is 0, 1 if the subdomain score is 2–4, and 2 if the subdomain score is 5–6. Scores for each of the five domains will be summed up to produce a composite IC index ranging from 0 (best possible ICI) to 14 (worst possible ICI).

Subsequently, this baseline ICI will be classified in four ways. First, using the terciles of ICI (TIC), ICI values less than or equal to the first tercile (Q1) will be classified as low TIC; ICI values between Q1 and the third tercile (Q3), including Q3, will be classified as medium TIC; and ICI values above Q3 will be classified as high TIC. This analysis model is explicitly shown in Figure 1.

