Second, the change in the ICI value during the follow-up time in the cohort will be measured and referred to as “ICI delta” (∆IC). The ∆IC is calculated as the difference between the ICI measured in the last follow-up wave minus the ICI measure at the baseline (variable with values between 0 and 10). Third, we will consider the presence of a decline in IC (DIC) if one or more declines in an IC domain are found from the baseline measure. As an example of IC domain decline in the cognitive dimension, a Montreal Cognitive Assessment (MoCA) score of 22 at follow-up versus 27.0 at baseline is considered a decline and probable “dementia” (Nasreddine et al., 2005). The opposite will be classified as no decline.

Finally, a weighted measure of IC (WIC) will be derived from the multivariate regression result of the association between IC subdomains and IADL loss, which will be adjusted for individual sociodemographic factors (see the Analysis section below for detailed description of WIC).

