### Generation of weighted IC score (WIC)

To build the weighted IC score (WIC), first, associations between subdomains of IC domains (sensory, mobility, vitality, cognitive, and psychological) and IADL loss will be evaluated by IADL models in a two-stage logistic regression (Meng et al., 2022). For this purpose, IC subdomains will be dichotomized, such as body mass index (BMI) (overweight–obese v. normal–underweight) and handgrip strength (normal–strong v. weak), both of which are subdomains of the vitality domain (Chen et al., 2020). The first stage of modeling requires bivariate analysis between each IC subdomain and IADLs to identify candidate subdomains to enter the multivariate logistic model (Meng et al., 2022). For this, the variable in the model whose *p-*value for the statistical test of association (chi-square) with IADL is less than or equal to α = 0.25 will enter the multivariate logistic regression model with adjustment for the sociodemographic, comorbidity, behavioral, and clinical factors. An exception will be variables selected *a priori* since they are clinically fundamental, such as BMI from the vitality domain.

In the multivariate logistic regression model, subdomains whose *p-*values are less than or equal to α = 0.05 (statistically significant) will be used to generate WIC as follows. For the regression coefficient in the multivariate model that reaches statistical significance (*p ≤* 0.05), its component will be transformed into a subdomain score by dividing the coefficient by the smallest regression coefficient in the model after rounding the absolute value of the coefficient to the nearest integer value. Regression coefficients that are not statistically significant in the adjusted model will have a value of one (1) point. A summary WIC will be obtained by adding points from all regression components. The subdomain terms will enter the multivariate regression model such that the higher the WIC score, the better the IC.

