#### Statistical models to assess whether IC is a predictor of ADLs/IADLs, falls, and death

Two Cox regression models will be evaluated to estimate the incidence rates of outcomes (i.e., functional loss measured by IADLs, falls, and death) associated with IC at baseline (e.g., TIC, DIC, and WIC) (ElHafeez et al., 2021). Cox’s first model has the indicator variable X to denote the association with each of the two groups of IC exposure at baseline (e.g., X1 = 1 for medium and high TIC and X1 = 0 for low TIC), with Y being the adverse incident at 3 years of follow-up (loss of ADLs/IADLs, falls, and death); survival times will be measured by the interval from the first assessment to the adverse incident. For subjects who do not experience an adverse incident, the follow-up time will be the last evaluation of the study.

The model also comprises a collection of covariates V with the potential to be a confounding factor in the association between Y and X (e.g., sociodemographic factors), and W would be the potentially interactive term between X and V (e.g., sex * TIC). The regression coefficient of X describes the effect of TIC on outcome Y, that is, the risk of greater or lesser loss of ADL/IADL, falls, and death for those exposed to medium or high TIC relative to those exposed to low TIC. The W terms will assess whether there is a positive interaction between TIC and one of the V confounders that have been identified to be potentially interacting. The model will extend by substituting TIC for DIC or WIC as the main exposure variable X. Alternatively, we can also model Y (e.g., IADL) as a function of X (either TIC, DIC, or WIC) and the same set of V and W using logistic regression to estimate the odds ratio of the outcomes.

We will evaluate the IC trajectory through changes in IC scores (∆IC or WIC) or the presence of IC decline (DIC) after 3 years, along with their associations with IADL outcomes, falls, and death. For example, the mean/median of ∆IC (or WIC) and the prevalence of DIC will be generated at baseline and at the end of the 3-year follow-up. We will then generate the mean/median or prevalence of IC measure by levels of ADL/IADL, falls, and death. The means/medians of IADLs and the incidence of falls and death after 3 years of follow-up will also be estimated.

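### Comorbidity is both an item of the IC index and an adjustment factor, so the adjusted question 2 coefficient is not the effect of the index as built and the WIC weight of the morbidity item depends on how the covariate is coded

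*Protocol article*

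**What the plan says.** **Comorbidity as part of IC.** Table 3 of the protocol article (under Dependent variables) lists "Number of chronic morbidities" as a binary vitality item, scored 1 from two diseases upward. The section on the IC composite index (ICI) repeats this: "vitality (subdomains comorbidity, medication, biomarkers, pain, strength, and nutrition") are summed, recoded and added into the index.

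**Comorbidity as adjustment factor.** Under Research questions and hypotheses to test, all three questions are to be answered regardless of "individual sociodemographic, behavioral, and clinical factors, and comorbidities". The comorbidity source cited there is also cited in Table 3 for the vitality item. Under Generation of weighted IC score (WIC), subdomains passing the first screen "will enter the multivariate logistic regression model with adjustment for the sociodemographic, comorbidity, behavioral, and clinical factors".

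**Less definite places.** The composite-index section describes the WIC regression as one "which will be adjusted for individual sociodemographic factors", with no mention of comorbidity. For the Cox and logistic outcome models the text says "The model also comprises a collection of covariates V with the potential to be a confounding factor". That set is open, and its only example is sociodemographic. In the quality-of-life and physical-activity model, IC decline is the dependent variable: "A slope coefficient of IC (Y = 1 if DIC = 1 or more declines".

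**The concern.** If a component of the exposure is also a covariate, the exposure coefficient compares people who are alike on that component. The Objectives section wants the composite index validated as a risk indicator. A coefficient with the morbidity part held fixed describes something else, and the article does not say which of the two it wants.

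The WIC regression is more exposed, because its scoring rule turns coefficients and p-values directly into points, and a non-significant item gets 1 point by default. A covariate that nearly duplicates an item can therefore change that item's weight for reasons unrelated to its importance for IADL loss. The term for clinical factors is not defined. If it takes in medications, pain, biomarkers or BMI, all of which are vitality items, the same problem spreads to them.

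**Working it through.** The article gives no figure on this point: no comorbidity prevalence, no correlation between items, no comorbidity effect. The structure can be checked from the text. Sizes can only be illustrated under stated assumptions.

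**1. Where the overlap bites**

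| Analysis | Role of IC | Comorbidity named as covariate? |
|---|---|---|
| Question 1 (change in ICI) | outcome | yes, in the question |
| Question 2 (ADL/IADL, falls, death) | exposure | yes in the question; not named in the Cox/logistic covariate set |
| WIC regression | items are the predictors | yes in the WIC section; sociodemographic only in the index section |
| Quality-of-life/activity model | outcome (IC decline) | yes |

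The exposure argument applies only to the second and third rows.

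**2. Question 2.** Let C be the morbidity item and X the IC group. The adjusted model has linear predictor a + bX + cC, and X is a function of the index, which contains C. So b compares two people with the same C, and the part of X that comes from C cannot vary.

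How much this matters was simulated. Assumptions: 14 binary items; latent correlation 0 to 0.4; comorbidity prevalence 40% or 60%; log-odds 0.14 per other item and 0 to 1.0 for comorbidity; outcome risk 6%; worst-ICI group against the rest; a vitality sum of 1, which the recoding rule leaves out, coded as 1.

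- Uncorrelated items (overlap alone): the relative risk falls at most from 1.44 to 1.39, and (1.44 − 1.39)/1.44 = 3.5%.
- Correlated items: the fall runs from 1.78 to 1.74 (2%) up to 3.00 to 1.95 (35%).
- Index rebuilt without the morbidity item, same adjustment: the adjusted relative risk is within about 0.02 of the full-index value throughout (for example 2.03 against 2.05).

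Most of the fall therefore comes from adjusting for a correlated risk factor, and little from the double use.

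**3. WIC regression.** If the covariate were the same binary variable M, the model would contain b1·M + b2·M = (b1 + b2)·M. Only the sum is identifiable, so the item has no weight of its own.

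If the covariate is a disease count, the result depends on how risk follows disease. Assumptions: 200 runs of 5,500 people; Poisson-type counts with base mean 1.5 or 2.2; one other subdomain item; log-odds 0.5 at the threshold, or 0.25 per disease.

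| Risk follows | Base mean | Coefficient without → with count | SE without → with | Share significant at 0.05, without → with |
|---|---|---|---|---|
| threshold (≥2) | 1.5 | 0.50 → 0.51 | 0.08 → 0.13 | 1.00 → 0.97 |
| threshold (≥2) | 2.2 | 0.51 → 0.53 | 0.09 → 0.12 | 1.00 → 1.00 |
| count | 1.5 | 0.56 → −0.01 | 0.08 → 0.12 | 1.00 → 0.03 |
| count | 2.2 | 0.67 → 0.00 | 0.08 → 0.11 | 1.00 → 0.08 |

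Standard error ratios in the threshold rows: 0.13/0.08 = 1.6 and 0.12/0.09 = 1.3. In the count rows the item would be non-significant in 92–97% of runs and get the default 1 point. How many points that costs depends on the ratio of its coefficient to the smallest one in the model, which the article cannot tell us.

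**The case against.** The adjustment is deliberate. The Rationale cites studies in which IC predicted decline in daily activities after adjustment for chronic disease, and the questions ask for an effect regardless of comorbidity. Comorbidity is a plausible common cause of impairment in other domains and of the outcomes, so an unadjusted estimate could be too large. This stands. It is a reason to keep comorbidity adjustment somewhere in the plan, though not to keep the item in the index at the same time.

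A reader might infer that the IC effect is underestimated, and by a sizeable amount. With all items on one common factor (loading 0.5) and every impairment equally harmful, the worst-tercile log odds ratio falls from 1.11 to 1.00 with the morbidity item as covariate, and to 0.97 with a continuous comorbidity score, a drop of 10–13%. The documents do not support reading this as bias. A smaller conditional coefficient answers a different question, and the check above attributes only about 0–4% of the relative risk to overlap. Nor would it threaten the study: taking 13% off the log of the planned mortality relative risk of 1.66 leaves about 1.55, and with 2,337 per group (2,750 less 15%) power is still 0.81 at 1.4.

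A reader might also infer that every hypothesis is affected. Question 1 and the quality-of-life model have IC as the outcome, so no exposure is being adjusted away there. Overlap between a covariate and the outcome is a separate matter, not argued here.

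Finally, only one of 14 items is certainly involved, and it changes the vitality code only at a category boundary. This limits the effect on the ICI. It does not help the WIC, where the item has its own weight.

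**Conclusion.** The concern holds in a limited form. Comorbidity has two roles, and the article does not say how they fit together. For question 2, the adjusted coefficient is not the effect of the index as built. Whether that is a fault depends on whether total IC or IC beyond comorbidity is wanted, which is not stated. In the simulated range the double use itself changes the relative risk little, so the issue there is mainly one of interpretation.

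For the WIC, the weight of the morbidity item depends on the coding of the covariate. It can drop to the default point, keep its coefficient with a standard error about 1.3–1.6 times larger, or be unidentifiable. The two descriptions of the WIC adjustment set also disagree.

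The direction and size of any bias in the IC effect are not established. All sizes rest on assumed prevalences, correlations and effects, and the WIC simulation used one other item in place of thirteen.

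**What to change.** 1. **WIC regression.** Do not enter comorbidity, or any clinical factor that is itself an IC item, as a covariate alongside the subdomain items. Define clinical factors accordingly, and make the composite-index section and the WIC section give the same adjustment set.
2. **Question 2.** Use comorbidity on one side only, in two labelled analyses: (a) the full index, not adjusted for its own items (total IC); (b) an index rebuilt without the morbidity and medication items, adjusted for the comorbidity score (IC beyond comorbidity). State which one answers the question as posed, and list the covariates of the Cox and logistic models to match.

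The cost is a change of wording and one additional analysis; the article states that no data have been collected. The downside is that the full-index estimate no longer claims independence from comorbidity. Analysis (b) carries that claim.
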